## Risks / Benefits

Based on the current evidence summarised above and the improved operation techniques, we hypothesise that a shorter AP duration (single-dose, as recommended for TURP by the EAU guidelines) does not result in more complications for the patients (see also Section “11.2 Determination of Sample Size” for detailed estimations).

Intervention or control have both shown good tolerability in clinical routine already. TMP/SMX (i.e. Cotrimoxazole) is a routinely used antimicrobial substance recommended in international and in-house guidelines as AP in TURP and UTI treatment, which is well tolerable and effective. AEs due to study medication should potentially be less common in the intervention group due to the lower exposure (single-dose vs 3-day course). Main AEs are skin reactions and gastrointestinal disorders according to the Swissmedic package leaflet. Patients with a known allergy or contraindications against TMP/SMX are excluded from the study participation. In case of such a severe reaction to TMP/SMX, the administration of study medication will be stopped immediately and necessary treatment of the allergic reaction will be performed. Continuation of the surgery and application of another AP is decided by the surgeon and the anaesthetist. The placebo contains small amounts of lactose. In case of a known intolerance, patients are excluded from the study. In case of AEs, the administration will be stopped and necessary treatment of the reaction will be performed.

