# STUDY OUTCOMES

All outcomes are events within 30 days (±5 days) after randomisation if not otherwise stated.

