### 6.2.2 Blinding procedures

The tailoring and randomisation of the study medication will be performed by the Hospital Pharmacy of the University Hospital Basel according to Good Manufacturing Practice. Perioperative AP will be two intravenous ampoules of TMP/SMX 400/80 mg (Bactrim Inf Konz^®^) solved in 250 ml sodium chloride short infusion in both groups. Each study medication package consists of either five tablets of placebo (Group A) or five tablets of TMP/SMX (Nopil forte^®^) 800/160mg (Group B) using licensed product repacked in a new immediate container which is blinded.

The placebo tablets are optically similar, but not identical to the TMP/SMX (Nopil forte^®^) 800/160mg. The blinding is ensured via non-transparent immediate containers. Perfectly identical placebos were not available.

After randomisation, the study team will provide the corresponding medication number to a nurse who is responsible for drug distribution. This nurse will bring the study medication to the patient and instruct the patient when to take the tablets.

Patients will then take the study drug independently according to the instruction of the nurse and an information sheet handed out with the pill container. The nurse will regularly ask if the study drug was taken and will document this information in the hospital information system. On day 3, the study nurse will acoustically check whether the container is empty. Drug containers which are not empty will be sent back to the Hospital Pharmacy of the University Hospital Basel, where the remaining tablets will be counted (the information will be recorded in the eCRF) and destroyed.

Evaluation of the primary outcome parameter will be done by an independent and blinded outcome assessor.

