### Assessment of safety outcomes

#### 9.2.4.1 (Serious) Adverse events

To assess any potential harms, the study team evaluates SAE according to the ICH E2A guidelines (38) as “definitely”, “probably”, “possibly”, “unlikely” and “not related”. The “Common Terminology Criteria for Adverse Events”, Version 5.0 terminology is going to be used for (S)AE occurring throughout this study: 1 – Mild (does not influence activities of daily living), 2 – Moderate (influences activities of daily living), 3 – Severe (makes some activities of daily living impossible), 4 – Life-threatening, 5 – Death. For further information please refer to Section 10.1.1. The study personnel will automatically be reminded at any study visit (planned or unplanned) from the time point of final treatment allocation to assess SAE on a separate form if any occurred. At day 3, AEs of special interests (e.g. diarrhea, nausea, vomiting, allergic reaction, and neurological disorder) will be assessed. Additionally, other not pre-specified AEs can be entered into the eCRF.

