### 9.3.2 Allocation

Before the randomisation takes place, each patient will undergo a final eligibility check based on all at that time point available evidence from the laboratory and from asking the patient (i.e. evidence for UTI, cfu ≥10^5^/ml or antibiotic treatment in the last 7 days before surgery (i.e. randomisation)). If all questions can be answered with no (i.e. no evidence for (i) UTI; (ii) cfu ≥10^5^/ml; (iii) antibiotic treatment in the last 7 days before surgery (i.e. randomisation)), the patient will be randomised and will receive an identification code number via eCRF. The assessed parameters from the surgery are listed under Section 9.1. In the evening after the operation the patients will receive a drug container with the study medication (i.e. 5 tablets). They will be instructed to swallow one tablet on the evening of day 0 and the consecutive 4 tablets on day 1 and day 2 (always one after breakfast and one after dinner). Nurses will remind the patients about the intake of each tablet. Patients get and information sheet with the dosage instruction.

### 9.3.3 Day 1 and 2

Nurses will remind the patients about the intake of each tablet.

### 9.3.4 Day 3

At day 3, a urine culture (with antimicrobial resistance pattern) is performed. Furthermore, AEs of special interest as well as other potential AEs will be assessed. The study nurse will check if the entire study medication was taken as prescribed (See section 8.4)

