### 10.1.3 Follow-up of (Serious) Adverse Events

During the study every step is taken to ensure, that all (S)AEs are identified and documented. Treating doctors and study centers are responsible to treat the (S)AEs and follow-up (S)AEs. At the routine follow-up at day 30 it is ensured, that all (S)AEs are identified and well treated. If a (S)AE occurs, all efforts will be undertaken to treat these (S)AEs (e.g. antiallergic treatment in case of an allergic reaction) and follow-up until it is resolved is ensured.

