## Determination of Sample Size

Sample size was estimated to be able to able to show non-inferiority of single-dose AP compared to 3-day AP with at least 80 % power (1 – *β* = 0.8) at a significance level of *α* = 5 %, applying a 1:1 randomisation scheme. A drop-out rate of 10% was considered.

Determination of the non-inferiority margin $\delta$: There is no direct data available describing the effect of 3-day AP with TMP/SMX versus placebo on our primary endpoint. Based on internal data from the involved clinics, we assumed an expected UTI rate within 30 days under usual care (3-day AP) of 0.09 (9 %). A comprehensive meta-analysis (5) reported an overall risk ratio (RR) for symptomatic UTIs treated with AP versus placebo of 0.38. Applied to an expected UTI rate under 3-day AP of 9%, this corresponds to an expected (hypothetical) UTI rate under placebo of 23.68% (i.e. 0.2368 * 0.38 = 0.09) and an expected absolute treatment effect (absolute risk reduction, ARR) of 3-day AP versus placebo (M1) of 14.68% (ARR = 0.2368 – 0.09 = 0.1468). The non-inferiority margin was determined in order to preserve 70% of M1 (i.e. ARR*0.7; 10.28% on an absolute scale), which was judged a clinically important fraction. This would correspond to an absolute event rate under 1-day AP versus placebo of 13.4% (i.e. 0.2368 – 0.1028 = 0.134). Assuming an event rate of 0.09 (9 %) in both trial arms, this resulted in a non-inferiority margin $\delta$ = 4.4% (i.e. 13.4% - 9%).

In other words, when 100 patients undergoing TURP or GL would receive no treatment, 24 (i.e. 23.68%) would have a symptomatic UTI and 76 patients not. Would all these 100 be treated with 3 day AP, 9 (i.e. 9%) would still have a symptomatic UTI and 91 not. Would all these 100 be treated with a single AP (which still has 70% of the effect), approximately 13 patients would have a symptomatic UTI and 87 not.

We would consider it acceptable when approximately 4 more of 100 patients would have an UTI when bearing in mind that these 4 UTIs can be treated relatively straightforward with antibiotics and that simultaneously the use of AP can be strongly decreased in all 100 treated patients. This also very likely leads to fewer individual adverse events and resistant pathogens, and beyond this has important beneficial consequences for public heath due to lesser antibiotic resistance in general.

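### The day-3 adverse event examples omit skin reactions, which the protocol names first among the drug's main adverse effects; recording rules vary in strength, and events before the first tablet are not set apart

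*Protocol*

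**What the plan says.** Section 3.7 (Risks / Benefits) identifies the expected harm of the study drug: "Main AEs are skin reactions and gastrointestinal disorders according to the Swissmedic package leaflet". It expects fewer such events in the single-dose arm because exposure is lower.

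Section 9.2.4.1 describes what is asked: "At day 3, AEs of special interests (e.g. diarrhea, nausea, vomiting, allergic reaction, and neurological disorder) will be assessed". It continues: "Additionally, other not pre-specified AEs can be entered into the eCRF".

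Two other places set the recording duty. Section 9.3.4 (Day 3) says: "Furthermore, AEs of special interest as well as other potential AEs will be assessed". Section 10.1.3 says: "During the study every step is taken to ensure, that all (S)AEs are identified and documented".

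On timing, the schedule in 9.1 ticks the adverse event row at day 3 only, while serious adverse events are ticked at every time point from day 0. Section 5 sets the counting window: "All outcomes are events within 30 days (±5 days) after randomisation if not otherwise stated". Randomisation takes place on the day of the operation. Both arms receive the same infusion, and the arms first differ with the evening tablet (6.2.2, 8.1.1, 8.1.2).

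Section 11.4.5 plans frequencies and percentages per arm for safety, with no tests. Section 11.2 uses the expected reduction in harm as one argument for tolerating about four more infections per 100 patients: "This also very likely leads to fewer individual adverse events and resistant pathogens".

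**The concern.** The trial weighs a possible small increase in infections against less antibiotic exposure and less harm. The harm side should therefore be measured as evenly as the protocol allows. Three features work against that.

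First, of the two main drug effects named in 3.7, gastrointestinal disorders have three prompts and skin reactions have none of their own. The nearest term, allergic reaction, asks the assessor for a judgement about cause, so a rash not judged allergic has no named place.

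Second, three sections describe the recording of other events with different force. Sites that follow different sections could record differently.

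Third, the count runs from randomisation. Nausea, vomiting or neurological events that begin before the first evening tablet come from influences common to both arms, such as anaesthesia, surgery and the infusion. They enter the same total as later events, which can differ by arm.

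At stake is the precision and completeness of the adverse event comparison. The non-inferiority conclusion is not affected.

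**Working it through.** **Main effects against prompts**

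| Main effect in 3.7 | Named in the 9.2.4.1 examples |
| --- | --- |
| Skin reactions | Not named; allergic reaction covers part |
| Gastrointestinal disorders | Diarrhoea, nausea, vomiting |

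**Recording duty for events outside the list**

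| Section | Force |
| --- | --- |
| 9.2.4.1 | Entry is possible |
| 9.3.4 | Assessment will be done at day 3 |
| 10.1.3 | All events identified and documented |

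**When events are captured.** In 9.1 the adverse event row is ticked at day 3 alone. Sections 9.3.6 and 10.1.3 also refer to day 30 in general terms, but the schedule shows no adverse event assessment there. An event missed on day 3 therefore has no second scheduled capture.

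**Inputs for the illustration.** The protocol gives no adverse event rate, so there is no figure of its own to reproduce on this point. The only input taken from it is the sample size: 1416 evaluable patients, so 1416 / 2 = 708 per arm. That figure does reproduce. With 9% in both arms, a 4.4% margin and the continuity-corrected Wilson interval, exact power at 1416 is 0.802, and 1416 / 0.9 rounds up to 1574. All rates below are assumptions.

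**Shared background.** Assume true gastrointestinal rates of 5% (3-day) and 2% (single dose). Let a background event have probability b in both arms, independent of the drug effect. Per patient:

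- observed rate = b + (1 − b)p
- risk difference = (1 − b)(0.05 − 0.02)
- half-width = 1.96 × √[(p₁(1 − p₁) + p₂(1 − p₂)) / 708], with p₁ and p₂ the observed rates

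| b | Observed rates | Difference (points) | Ratio | 95% half-width (points) |
| --- | --- | --- | --- | --- |
| 0% | 5.0% vs 2.0% | 3.0 | 2.50 | 1.9 |
| 5% | 9.8% vs 6.9% | 2.9 | 1.41 | 2.9 |
| 10% | 14.5% vs 11.8% | 2.7 | 1.23 | 3.5 |
| 20% | 24.0% vs 21.6% | 2.4 | 1.11 | 4.4 |
| 30% | 33.5% vs 31.4% | 2.1 | 1.07 | 4.9 |

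For b = 20%: 0.20 + 0.80 × 0.05 = 0.240 and 0.20 + 0.80 × 0.02 = 0.216. The half-width is 1.96 × √[(0.240 × 0.760 + 0.216 × 0.784) / 708] = 0.044. The difference shrinks modestly, and the larger effect is the wider interval.

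Restricting to onset after the first tablet removes only the background that began earlier. The step from the 20% row to the 0% row is thus the most that could be gained under these assumptions.

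**Skin reactions.** Assume true rates of 3% versus 1%. If 90% are recorded, 2.7% versus 0.9% gives a difference of 1.8 points. If 50% are recorded, 1.5% versus 0.5% gives 1.0 point. Both the rates and the capture fractions are assumed.

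**The case against.** The strongest reply has five parts.

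- **The form.** The list is introduced as examples, it includes allergic reaction, and the case report form is not in the document. A reader might infer that the day-3 form has no prompt for skin reactions. The document does not show that. It shows only that the protocol does not name them. This part of the reply stands.
- **Optional recording.** A reader might also infer that other events are optional. Section 9.3.4 says that they will be assessed and 10.1.3 says that all are documented. The permissive sentence in 9.2.4.1 may mean only that a field exists. What remains is a difference in wording that should be removed.
- **Nausea and vomiting.** It is tempting to say that these cannot depend on the arm. That is true only before the first evening tablet. By day 3 patients are due to have taken five tablets of drug or placebo, 3.7 names gastrointestinal disorders as a main drug effect, and the evidence review in section 3.4 reports nausea and vomiting as seemingly more common with 3-day prophylaxis in a small earlier trial of another antibiotic. Prompting for them is right.
- **Assumed rates and no tests.** Every rate in the illustration is assumed, and 11.4.5 plans no safety tests, so power is not the relevant measure. This stands, which is why only differences, ratios and interval widths are shown. The ratio also exaggerates the loss: it falls from 2.50 to 1.11 while the difference falls only from 3.0 to 2.4 points. Skin or allergic events tabulated by type are not diluted at all.
- **The margin.** The 4.4% comes from preserving 70% of the estimated prophylaxis effect. Fewer adverse events is a supporting argument, and the non-inferiority decision uses no adverse event data. This too stands.

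The choice of safety tables may also belong in an analysis plan that is not shown. Onset relative to the first tablet, however, can be tabulated only if it is collected, so it has to be settled when the form is designed.

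**Conclusion.** The point holds as one about capture and precision. The protocol names skin reactions first among the drug's main adverse effects and then leaves them out of the day-3 examples, at the only visit where its schedule ticks adverse events. A rash not labelled allergic may be recorded less completely than the prompted gastrointestinal events. Sections 9.2.4.1, 9.3.4 and 10.1.3 differ in how firmly they require other events to be recorded. Events before the first evening tablet add shared background and are not distinguished from later ones.

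The document does not support the further inference that the comparison of harm is biased between arms or lost. The background is balanced by randomisation; it widens the interval and slightly dilutes a pooled or gastrointestinal total.

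The size is unknown. Under assumed rates of 5% versus 2%, 708 per arm and a 20% background independent of the drug effect, the difference goes from 3.0 to 2.4 points and the half-width from 1.9 to 4.4 points. A smaller background, or one arising mostly after the first tablet, would make the gain from separating onset smaller.

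**What to change.** - In 9.2.4.1, add skin reaction (rash, itching) by name to the day-3 events of special interest, separate from allergic reaction.
- Align 9.2.4.1, 9.3.4 and 10.1.3 so that all three say other adverse events must be recorded.
- For each adverse event, record whether it began before or after the first oral tablet, or the scheduled time of that tablet if none was taken.
- In the safety summary, tabulate adverse events by type, with a row for onset after the first tablet beside the row for all events since randomisation.

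The cost is one prompt, one tick box and one table row, with a slightly longer day-3 form. Treatment, the primary analysis and the sample size are unchanged.

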#### Laboratory parameters

Please refer to Section 9.2.1 and 9.2.2.

#### Vital signs

Please refer to Section 9.2.1 and 9.2.2.

### 9.2.5 Assessments in participants who prematurely stop the study

As the vast majority of outcomes is based on routinely collected data, outcomes can also be assessed if participants prematurely stop the study.

## Procedures at each visit

### See also Section 9.1.

### 9.3.1 Enrolment

For each patient at enrolment (approximately 7 days before surgery): eligibility screen, informed consent and assessment of baseline variables (study site, study ID, BMI, ASA score, blood counts, anticoagulation, PSA, prostate volume, post voiding residual volume, catheterisation, International Prostate Symptom Score/Quality of Life score, history of urinary tract infections) is performed.

### 9.3.2 Allocation

Before the randomisation takes place, each patient will undergo a final eligibility check based on all at that time point available evidence from the laboratory and from asking the patient (i.e. evidence for UTI, cfu ≥10^5^/ml or antibiotic treatment in the last 7 days before surgery (i.e. randomisation)). If all questions can be answered with no (i.e. no evidence for (i) UTI; (ii) cfu ≥10^5^/ml; (iii) antibiotic treatment in the last 7 days before surgery (i.e. randomisation)), the patient will be randomised and will receive an identification code number via eCRF. The assessed parameters from the surgery are listed under Section 9.1. In the evening after the operation the patients will receive a drug container with the study medication (i.e. 5 tablets). They will be instructed to swallow one tablet on the evening of day 0 and the consecutive 4 tablets on day 1 and day 2 (always one after breakfast and one after dinner). Nurses will remind the patients about the intake of each tablet. Patients get and information sheet with the dosage instruction.

### 9.3.3 Day 1 and 2

Nurses will remind the patients about the intake of each tablet.

### 9.3.4 Day 3

At day 3, a urine culture (with antimicrobial resistance pattern) is performed. Furthermore, AEs of special interest as well as other potential AEs will be assessed. The study nurse will check if the entire study medication was taken as prescribed (See section 8.4)

### 9.3.5 Unscheduled Visits

Any unscheduled visits occurred during hospital discharge will be assessed at the 30 day follow-up by consulting the hospital information system and by asking the patient.

### 9.3.6 Follow-up after 30 days

All endpoints will be assessed at day 30 (±5 days; for more details see Section 9.2.1-9.2.4). In case that a patient will not conduct the 30 day visit, the treating physician or the study nurse will try to find an alternative date within the 5 day window. If this is not possible, the requested information for the primary endpoint will be asked by phone.

# SAFETY

## Drug studies

During the entire duration of the study, all SAEs are collected, fully investigated and documented in source documents and eCRFs. Study duration encompassed the time from when the participant signs the informed consent until the last protocol-specific procedure has been completed, including a safety follow-up period planned at close-out day 30.

### 10.1.1 Definition and assessment of (serious) adverse events and other safety related events

We follow the definition of the ICH E2A guidelines (39): “An **Adverse Event (AE)** is any untoward medical occurrence in a patient or a clinical investigation participant administered a pharmaceutical product and which does not necessarily have a causal relationship with the study procedure. An AE can therefore be any unfavourable and unintended sign (including an abnormal laboratory finding), symptom, or disease temporally associated with the use of a medicinal (investigational) product, whether or not related to the medicinal (investigational) product.

A **Serious Adverse Event (SAE)** is classified as any untoward medical occurrence that:

- results in death
- is life-threatening
- results in re-hospitalisation
- results in persistent or significant disability/incapacity

In addition, important medical events that may not be immediately life-threatening or result in death, or require hospitalisation, but may jeopardise the patient or may require intervention to prevent one of the other outcomes listed above should also usually be considered serious.” (ICH E2A)

Since all patients are adult men, “congenital anomaly/birth defect” will not be applicable for this trial.

Prolonged hospitalisation is common in the population of interest and is therefore not considered as an SAE.

SAEs should be followed until resolution or stabilisation. Participants with ongoing SAEs at study termination (including safety visit) will be further followed up until recovery or until stabilisation of the disease after termination.

Assessment of Causality

Both Investigator and Sponsor/Principle Investigator make a causality assessment of the event to the study drug, based on the criteria listed in the ICH E2A guidelines:

| Relationship | Description |
| --- | --- |
| Definitely | Temporal relationship  Improvement after dechallenge*  Recurrence after rechallenge  (or other proof of drug cause) |
| Probably | Temporal relationship  Improvement after dechallenge  No other cause evident |
| Possibly | Temporal relationship  Other cause possible |
| Unlikely | Any assessable reaction that does not fulfil the above conditions |
| Not related | Causal relationship can be ruled out |
| *Improvement after dechallenge only taken into consideration, if applicable to reaction | |

Unexpected Adverse Drug Reaction

An “unexpected” adverse drug reaction is an adverse reaction, the nature or severity of which is not consistent with the applicable Summary of Product Characteristics (SmPC) of Bactrim Inf Konz^®^ and Nopil forte^®^.

Suspected Unexpected Serious Adverse Reactions (SUSARs)

The Sponsor/Principle Investigator evaluates any SAE that has been reported regarding seriousness, causality and expectedness. If the event is related to the investigational product and is both serious and unexpected, it is classified as a SUSAR. If a SUSAR is suspected, the local investigator and the principle investigator are allowed to break the blinding in the EDC system. Unblinding will be documented in the EDC system.

Assessment of Severity

The “Common Terminology Criteria for Adverse Events”, Version 5.0 terminology is going to be used for adverse events occurring throughout this study: 1 – Mild, 2 – Moderate, 3 – Severe, 4 – Life-threatening, 5 – Death (40).

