## Safety Objectives

To evaluate the impact of a single-dose AP in comparison to a 3-day AP, in patients undergoing TURP or GL, on AEs and serious adverse events (SAEs).

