## Safety Outcomes

- AEs
- SAEs

All other relevant ‘safety outcomes’ (i.e. complications) are assessed as primary or secondary outcomes.

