## Criteria for withdrawal / discontinuation of participants

Enrolled patients have always the opportunity to withdraw from the trial without mentioning any specific reason at any time. In case of a SAE, the study drug will be stopped immediately and necessary treatment will be performed. In case of any complications, which require an antimicrobial therapy, the study drug will be stopped. Participations who stopped the study drug or withdrew consent will be asked if they are anyway willing to conduct the routine follow-up visit 30 days after surgery. Patients can state that they do not wish to be contacted for the study anymore and that also their physician shall not be contacted for outcome assessment.

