## Return or Destruction of Study Drug / Medical Device

All study drugs will be administered during the hospital stay. Unused study drugs will be destroyed by the Hospital Pharmacy of the University hospital Basel.

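### The blanket exclusion of prolonged hospital stay from the SAE criteria leaves a gap during the index stay, when all study drug is given; limit it to routine prolongation.

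*Protocol*

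**What the plan says.** Section 10.1.1 lists four criteria for a serious adverse event: death, threat to life, persistent or significant disability, and an event that "results in re-hospitalisation". It adds a clause for "important medical events that may not be immediately life-threatening or result in death, or require hospitalisation, but may jeopardise the patient", and says that such events should usually be treated as serious. It then removes one criterion outright: "Prolonged hospitalisation is common in the population of interest and is therefore not considered as an SAE". No rate supports the word common, and the text does not separate a stay lengthened by an adverse event from one lengthened by the ordinary post-operative course.

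Section 8.9 on return and destruction of study drug states: "All study drugs will be administered during the hospital stay". The schedule in section 9.1 places the tablets on days 0 to 2 and discharge on day 3.

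The safety objective is "To evaluate the impact of a single-dose AP in comparison to a 3-day AP, in patients undergoing TURP or GL, on AEs" and on SAEs. The section on safety outcomes names AEs and SAEs and adds: "All other relevant ‘safety outcomes’ (i.e. complications) are assessed as primary or secondary outcomes". Section 11.4.5 plans frequencies and percentages by arm, without tests.

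**The concern.** The reason given for the exclusion fits stays that run long as part of the usual course after surgery. It does not fit a stay lengthened by a suspected drug reaction or an infection, yet the sentence covers those too. The exclusion applies exactly while patients are exposed to study drug, which is when acute reactions to TMP/SMX are most likely to appear.

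SAE status also starts other processes. Under section 10.1.2, reporting to the sponsor within 24 hours and the annual safety report rest on it. Under section 10.1.1, SUSAR evaluation starts from a reported SAE. The protocol has no data safety monitoring committee (section 1.7) and no interim analysis (section 11.4.4), so SAE reporting carries most of the continuing safety oversight. A reaction that keeps a man in hospital but meets no other criterion can miss this route.

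**Working it through.** The protocol states no SAE rate and no rate of prolonged stay, so there is no figure to reproduce. The check is a reading of the rules, followed by an illustration of what they can and cannot do to the arm comparison.

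**1. Status of one event before and after discharge (section 10.1.1)**

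| Event | During the index stay | After discharge |
| --- | --- | --- |
| Fatal, life-threatening or disabling | SAE | SAE |
| Important medical event, by judgement | Usually SAE | Usually SAE |
| Serious only because it needs hospital care | Not an SAE by the hospital criterion | SAE if re-admitted |
| Managed without admission, no other criterion | Not applicable | Not an SAE |

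The asymmetry is confined to the third row.

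**2. Whether other data fill that row**

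- Infections: largely yes. Treated symptomatic UTI is the primary outcome, and urosepsis, pyelonephritis and the other infections are secondary outcomes.
- Drug reactions: largely no. The Risks / Benefits section names skin and gastrointestinal reactions as the main AEs. Apart from *Clostridium difficile*-associated infection, none is a listed primary or secondary outcome.
- Hospital days: recorded, but section 9.2.2 derives them from admission and discharge dates without a cause, so prolongation due to a reaction cannot be recovered from them.
- AEs: assessed at day 3 (sections 9.1 and 9.2.4.1) and graded for severity. A severity grade does not by itself start the 24-hour route.

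**3. Effect on the arm comparison**

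Inputs: 1574 recruited (section 11.2), so 1574 / 2 = 787 per arm. Assumed, because the protocol gives neither: a rate r of events serious only through hospital care, and a share s of them starting in the index stay. It is also assumed that such events after discharge lead to re-admission.

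Counted SAEs per arm = 787 × r × (1 − s).

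With r = 2% in both arms, the true number is 787 × 0.02 = 15.7 in each:

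| s in Group A | s in Group B | Counted A | Counted B | Ratio A/B |
| --- | --- | --- | --- | --- |
| 50% | 50% | 7.9 | 7.9 | 1.00 |
| 30% | 50% | 11.0 | 7.9 | 1.40 |
| 50% | 30% | 7.9 | 11.0 | 0.71 |
| 20% | 80% | 12.6 | 3.1 | 4.0 |
| 80% | 20% | 3.1 | 12.6 | 0.25 |

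With true rates of 2% and 3% (15.7 and 23.6 events) and s = 50% in both arms, 7.9 and 11.8 are counted. The ratio stays at 0.67, but the difference shrinks from −1.0 to −0.5 percentage points.

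Equal timing therefore lowers the counts and shrinks absolute differences but leaves the ratio alone. A biased ratio needs timing that differs by arm, and the sign follows the assumed shares.

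**The case against.** The strongest defence is that the sentence removes a long stay as a criterion but does not say that an event accompanied by a long stay cannot be serious. The important-medical-events clause remains open, and it extends to events that may need intervention to prevent another listed outcome, which includes re-admission. This stands, and it means that one cannot say an in-hospital event never counts. But the clause works by individual judgement, next to a sentence pointing the other way, at five sites.

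The defence adds that infections are captured elsewhere by intent. That also stands: the infection comparison does not rest on the SAE count. It does not extend to drug reactions.

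A third point is that section 10.1.2 has a separate 24-hour route for safety signals. It covers suspected new risks and relevant new aspects of known reactions that call for safety measures, so it reduces the gap without closing it.

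A reader might infer more: that the rule distorts the SAE comparison, and in favour of the single dose, because infections in Group B may be delayed until after discharge. The documents do not support this. The rule is the same in both blinded arms, and no data on onset are given. There is also a force in the other direction: only Group B takes oral TMP/SMX, all of it in hospital, and the Risks / Benefits section expects fewer drug-related AEs in the single-dose arm. Leaving in-hospital reactions uncounted would then flatter Group B. Nor is every infection after discharge an SAE. Section 9.2.1 names the general practitioner as the typical treating physician, and without re-admission the hospital criterion is not met.

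**Conclusion.** The point holds as a gap in capture. Followed as written, section 10.1.1 under-counts in-hospital SAEs whose only serious feature is that they lengthen the stay. These are chiefly suspected reactions to TMP/SMX, which can then also miss 24-hour reporting and SUSAR evaluation. The size cannot be derived, because the protocol gives neither the rate of such events nor how many would be reported as important medical events.

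Bias between the arms is a possibility of unknown direction, not a finding. In the illustration the ratio is 1.00 under equal timing and runs from 0.25 to 4.0 across the assumed shares, so no single pair of counts should be quoted as its magnitude. The primary non-inferiority analysis is untouched. This is a cheap improvement to safety reporting.

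**What to change.** Replace the sentence in section 10.1.1 with one limited by cause, for example: *Prolongation of the index stay for routine or logistic reasons (such as the expected post-operative course or social reasons) is not an SAE. Prolongation caused by an adverse event, including infection or a suspected drug reaction, meets the hospital criterion in the same way as re-hospitalisation.*

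Leave the re-hospitalisation criterion unchanged. Carrying a list of excluded causes over to it could drop re-admissions, for instance for bleeding or failed voiding, that count now.

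One dependency needs attention. The section on withdrawal and discontinuation states: "In case of a SAE, the study drug will be stopped immediately and necessary treatment will be performed". The Risks / Benefits section ties stopping to AEs instead. These two passages must be reconciled, since a change to what counts as an SAE also changes when the first one applies.

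The cost is one sentence, matching guidance on the SAE form, and a modest number of extra SAE reports. Discharge dates are already collected; the only new item is the cause of prolongation on the SAE form.
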